### Sample size calculation

This is an observational study aimed at investigating very rare complications, the incidence of which is difficult to estimate. Literature reports an incidence ranging from 0 to 2.8%, depending on the study and cohort considered [8].

The sample size estimation was performed using an approach based on the precision of the proportion estimate, defined as the total width of the confidence interval. For this purpose, the Agresti-Coull Wilson method was applied [9].

Starting from a cumulative incidence of 0.005 (0.5%) [10], with a 95% confidence level and aiming for a confidence interval width of 0.003, a minimum of 3,396 subjects must be enrolled. The estimation was conducted using the {presize} package of R software, version 4.3.3 (2024-02-29 ucrt).

When the study was initially planned, we anticipated enrolling at least 10 centers in the NEURAL study, with an expected average recruitment of approximately 350 patients per center over two years, making the achievement of the planned sample size a realistic goal.

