**Expected results:**

Based on an estimated complication rate of 0.5%, a minimum of 3,396 patients will be required to ensure adequate precision of incidence estimates. Nationwide participation is expected to exceed this target.

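### The planned 3,396 subjects give a 95% interval about 0.005 wide, not the stated 0.003; a width of 0.003 needs about 8,700 to 8,850 subjects

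*Protocol article*

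**What the plan says.** The Sample size calculation section of the protocol article bases the sample size on the precision of a proportion, "defined as the total width of the confidence interval". It takes a cumulative incidence of 0.005, "with a 95% confidence level", and then states: "aiming for a confidence interval width of 0.003, a minimum of 3,396 subjects must be enrolled". On the interval, it says that "the Agresti-Coull Wilson method was applied", and it reports that the R package presize was used. The section mentions no allowance for dropout or for clustering by center.

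The abstract, under Expected results, repeats the number without the width: "a minimum of 3,396 patients will be required to ensure adequate precision of incidence estimates".

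**The concern.** The sentence gives every input and the result, so it can be checked without outside information. At an incidence of 0.5%, 3,396 subjects means about 17 expected events (3,396 × 0.005 = 16.98). So few events cannot fix the incidence to within a total width of 0.3 percentage points.

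The primary objective is to estimate the composite incidence, and this sentence is the only quantitative support for the size of the study. If the width is wrong, a reader is promised a clearly tighter estimate than the declared minimum can give. The abstract's claim of adequate precision, and the precise incidence estimates promised under Expected impact on clinical practice, rest on the same figure.

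**Working it through.** **Inputs**, all from the Sample size calculation section: p = 0.005; 95% two-sided confidence, so z = 1.960 and z² = 3.841; target total width w = 0.003; stated n = 3,396. The method name joins two different intervals, so both were tried, with the Wald and exact (Clopper-Pearson) intervals for comparison.

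**Formulas for the total width**

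- Wald: w = 2z√[p(1−p)/n]
- Wilson: w = 2z√[p(1−p)/n + z²/(4n²)] / (1 + z²/n)
- Agresti-Coull: w = 2z√[p̃(1−p̃)/(n+z²)], with p̃ = (np + z²/2)/(n + z²)

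**Step 1. Try to reproduce 3,396.** The Wald formula can be solved by hand: n = 4z²p(1−p)/w² = 4 × 3.841 × 0.004975 / 0.000009 ≈ 8,494. The others were solved numerically.

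| Interval | n for width 0.003 | n for width 0.005 | Width at n = 3,396 |
|---|---|---|---|
| Wald | 8,494 | 3,058 | 0.0047 |
| Wilson | 8,676 | 3,233 | 0.0049 |
| Agresti-Coull | 8,853 | 3,395 | 0.0050 |
| Exact | 9,205 | 3,500 | 0.0051 |

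None of these methods gives 3,396 at a width of 0.003.

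**Step 2. The Agresti-Coull width at the stated n.** p̃ = (16.98 + 1.921)/(3,396 + 3.841) = 18.901/3,399.841 = 0.005559. The half-width is 1.960 × √(0.005559 × 0.994441/3,399.841) = 0.002499. The interval is therefore 0.00306 to 0.00806, with a total width of 0.0050.

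**Step 3. Other readings of the sentence**

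- *0.003 as a half-width (total width 0.006).* This gives 2,448 (Agresti-Coull) or 2,295 (Wilson). It also contradicts the section's own definition of precision as total width.
- *A lower confidence level.* Two-sided 90% gives 5,983 or more at width 0.003. Reaching 0.003 with 3,396 subjects would take a level of only about 78%.
- *A different target width.* Agresti-Coull at a total width of 0.005 gives 3,394.3, or 3,395 when rounded up. This is within one subject of 3,396 and is the only close match among the readings tried at the stated incidence and confidence level.

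**Step 4. Size of the discrepancy.** Width: 0.00487/0.003 = 1.62 (Wilson) and 0.00500/0.003 = 1.67 (Agresti-Coull). Sample size: 8,676/3,396 = 2.55 and 8,853/3,396 = 2.61.

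**Step 5. If the incidence is not 0.5%.** The Introduction hypothesises a higher incidence than registry data suggest, and the sample size section cites a range up to 2.8%. With 3,396 subjects the Agresti-Coull width is 0.0069 at 1% and 0.0112 at 2.8%.

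**The case against.** The strongest reply is that 3,396 is a minimum and the study expects to pass it. The initial plan of 10 centers with about 350 patients each gives 3,500, but 43 centers had joined at submission. With 43 centers, about 206 patients each would reach 8,853. This is a fair limit on the consequence: the shortfall applies at the declared minimum, and the width finally obtained is unknown. It does not repair the calculation, because a study that stopped at 3,396 could claim to have met its precision goal. Nor is the larger number assured. The figure of 350 per center was for two years, while the Study duration section limits each center to six months. If recruitment scales with time, that is 350 × 6/24 = 87.5 per center, or about 3,760 over 43 centers.

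It can also be said that no hypothesis test or power claim depends on the 0.003, and that joining two method names is loose wording which does not cause the mismatch. Both are true. They make this a correction of a stated figure and not a flaw in the design.

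How 0.003 came to be printed cannot be settled. It is close to the lower Agresti-Coull limit (0.00306), but equally close to the distance from 0.005 to the upper limit (0.0031). The match at a width of 0.005 is the likely explanation of the 3,396, not a documented one.

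**Conclusion.** The concern holds. The stated number and the stated width do not belong together under either interval the article names. At an incidence of 0.5% and 95% confidence, the declared minimum delivers a total width of about 0.005, 1.62 to 1.67 times the stated 0.003. Meeting 0.003 would take about 2.6 times as many subjects. Because this figure alone supports the sample size for the primary objective, it must be corrected.

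The calculation assumes independent observations, complete outcome data and a true incidence of 0.5%. The clustering by center that the article acknowledges would tend to widen the interval further, as would a higher incidence.

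**What to change.** In the Sample size calculation section, do one of the following.

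- **Keep 3,396** and state the target as a total width of 0.005, with an expected 95% interval of about 0.31% to 0.81% at an incidence of 0.5% (Agresti-Coull). This costs a corrected sentence and a less favourable stated precision. It needs no extra patients.
- **Keep 0.003**, if that precision is really required, and raise the minimum to 8,853 (Agresti-Coull) or 8,676 (Wilson). The abstract's number and the recruitment plan must then change too, because 10 centers with 350 patients each would not be enough.

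In either case, name one interval method and use it in the analysis as well. At a width of 0.005 the choice already matters: 3,395 with Agresti-Coull against 3,233 with Wilson. It would also help to give the expected width at 0.5%, 1% and 2.8% (0.0050, 0.0069 and 0.0112 with 3,396 subjects, Agresti-Coull).

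Under the first option the abstract needs no change, since it gives no width. The full protocol and the registry record should be checked for the same figure.

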### Study duration

The overall duration of the study will be two years.

To ensure adequate standardization, each center participating in the NEURAL study will recruit patients for a duration of six months following ethics committee approval (therefore, each center may recruit patients up to 180 days from the enrollment of the first patient at that center).

### Ethical approval and protocol registration

On May 15, 2025, the study received a conditional favorable opinion from the *Comitato Etico Territoriale Centro-Est Veneto* (Prot. 38516/2025). Subsequently, on September 18, 2025, an amendment was approved, authorizing the participation of the 46 centers currently involved in the study. A copy of the IRB approved protocol is available as S3 File in both original language (Italian) and English.

The study will be conducted according to the principles of the Declaration of Helsinki and subsequent amendments All patients must provide written informed consent prior to inclusion in the study, moreover,in order to comply with the legal provisions set forth by Good Clinical Practice regulations (Legislative Decree 211/2003) and in accordance with the laws and regulations regarding personal data protection pursuant to Article 13 of EU Regulation 679/2016 (GDPR) [11], each patient will receive information about the study and be asked to provide written informed consent for the processing of personal data.

### Additional risks or benefit for the patient

There are no additional risks or benefits for the patient considering the observational design of the study.

### Publication and authorship policy

The Steering Committee will oversee the statistical analysis and synthesis of the collected data and will draft the manuscript for submission to a peer-reviewed journal. Each center will appoint local coordinators responsible for ensuring all necessary ethical and regulatory approvals are obtained, protocol adherence during the study period, and the integrity and completeness of collected data. To recognize the significant contributions of all participating centers and researchers, an Authors’ Group will be established under the name “SIAARTI Study Group.” The final publication of the study results will acknowledge the contributions of all members of the SIAARTI Study Group. Collaborators and authors will be duly recognized, and their contributions will be traceable through major scientific databases such as PubMed and Scopus.

## Discussion

### Study significance

Regional anesthesia is considered one of the safest anesthetic techniques, offering significant advantages in perioperative pain management and recovery. However, although major complications such as nerve injury, hematoma, pneumothorax, and LAST are rare, their true incidence remains uncertain [12]. Current estimates largely rely on registry data and retrospective analyses, which often suffer from limited sample sizes, heterogeneous reporting, and inconsistent definitions of adverse events [13].

The NEURAL study is designed to provide a comprehensive and prospective evaluation of these complications, contributing new evidence on their prevalence and associated risk factors. By collecting standardized data from a large multicenter cohort, this study will help refine current knowledge about the real-world safety of regional anesthesia and elucidate the mechanisms underlying neurological and systemic adverse events.

### Strengths and limitations

A key strength of the NEURAL study lies in its multicenter, prospective, and observational design, coordinated under the auspices of SIAARTI. The inclusion of multiple tertiary centers across Italy ensures broad representation of clinical practice, patient demographics, and procedural variability, thereby enhancing the generalizability of results.

The study’s standardized definitions of complications and structured follow-up at 24 and 48 hours, as well as at 15 and 30 days—with extended follow-up up to one year for nerve injury—will enable accurate detection of both early and delayed complications. The detailed recording of procedural variables (e.g., ultrasound guidance, injection pressure, adjuvants used) and patient characteristics (e.g., comorbidities, anticoagulant use) allows for in-depth risk factor analysis using multivariable modeling.

However, the study also has inherent limitations. As an observational protocol, it cannot establish causal relationships between regional anesthesia and complications. Additionally, the identification of rare events may still be constrained by the sample size, despite careful power calculation. Potential variability in operator experience and institutional practices may introduce confounding, though standardized definitions and training across centers are intended to minimize this effect.

### Expected impact on clinical practice

The NEURAL study aims to generate high-quality, real-world data that can directly inform clinical practice. By providing precise estimates of complication incidence and identifying modifiable risk factors, it may lead to more targeted preventive strategies, improved patient counseling, and optimization of regional anesthesia techniques. Furthermore, understanding the multifactorial nature of nerve injury—beyond direct mechanical trauma—could influence educational priorities, procedural guidelines, and device development for safer block performance.

Ultimately, the findings of the NEURAL study are expected to strengthen the evidence base supporting the safety of regional anesthesia, guide individualized risk assessment, and promote continuous quality improvement within anesthesiology practice.
